## Abstract

**Background:**

Mobility problems are present in 70–80% of stroke survivors and can result in impaired gait and reduced physical activity limiting independent living. Auditory rhythmic cueing (ARC) has been used to provide auditory feedback and shows promise in improving a variety of walking parameters following stroke. The aim of this pilot study is to assess the feasibility of conducting a multi-centre, observer blind, randomised controlled trial of auditory rhythmical cueing (ARC) intervention in home and community settings in North East England.

**Methods:**

This pilot observer blind randomised controlled feasibility trial aims to recruit 60 participants over 15 months from community stroke services in the North East of England. Participants will be within 24 months of stroke onset causing new problems with mobility. Each participant will be randomised to the study intervention or control group. Intervention treatment participants will undertake 18 auditory rhythmical cueing (ARC) treatment sessions over 6 weeks (3 × 30 min per week, 6 supervised (physiotherapist/research associate)/12 self-managed) in a home/community setting. A metronome will be used to provide ARC during a series of balance and gait exercises, which will be gradually progressed. The control treatment participants will undertake the same duration balance and gait exercise training programme as the intervention group but without the ARC. Feasibility will be determined in terms of recruitment, retention, adverse events, adherence, collection of descriptive clinical and accelerometer motor performance data at baseline, 6 weeks and 10 weeks and description of participant, provider and clinical therapists’ experiences. As well as using questionnaires to collate participant views, qualitative interviews will be undertaken to further understand how the intervention is delivered in practice in a community setting and to identify aspects perceived important by participants.

**Discussion:**

The ACTIVATE study will address an important gap in the evidence base by reporting whether it is feasible to deliver auditory rhythmical cueing in the home and community to improve gait and balance parameters following stroke. The feasibility of the study protocol will be established and results will inform the design of a future multi-centre randomised controlled trial.

**Trial registration:**

Trial register: ISRCTN, Trial identifier: ISRCTN10874601: Date of registration: 12/03/2018.

## Background

Mobility problems are present in 70–80% of stroke survivors [1], often resulting in impaired gait, which persists despite rehabilitation [2], and reduced physical activity [3]. There are 1.2 million stroke survivors in the UK alone [4], equating to around 840,000 to 960,000 people currently struggling with mobility problems. Gait impairments commonly observed include reduced walking speed, decreased stride length/cadence [5, 6] and increased temporal asymmetry [7], which limits home and community ambulation and is associated with increased dependency and reduced quality of life [8]. Discovering treatments that target gait impairment, balance and mobility are viewed as one of the top priorities in life after stroke [9].

A recent systematic review [10] examined the use of auditory rhythmical cueing (ARC) in motor rehabilitation. ARC provides auditory feedback usually delivered via music or metronome [11, 12] to improve gait and physical activity post-stroke. This review found that stroke patients showed significantly greater walking velocity and improvements in cadence and stride length after intervention with ARC compared to control groups receiving traditional rehabilitative or other types of intervention. Several other systematic reviews on the use of ARC in motor recovery after stroke reported promising results finding improvements in selected gait parameters [2, 11, 13]. The benefit of ARC-based gait interventions include implementation during functional tasks in home and community settings, sustained walking practice in urban and rural environments and overall increased task practice (a recognised key component in recovery post-stroke) [12, 14].

Much of the work to date on ARC has been ward or laboratory based, with many studies using treadmill walking [2, 15], limiting application of findings to ‘real world’ ambulation. One recent study however has addressed the feasibility and potential efficacy of a home-based ARC training programme for stroke survivors and reported that this was feasible and well tolerated [16]. However, whilst finding improvements in walking and functional mobility, the training involved stepping in place/marching on the spot and these activities may not translate to community mobility. Although targeting gait in the home is important, walking in the community is a key activity for stroke survivors which, for many, is still unachievable and as a result they are confined to home [17, 18]. Developing an ARC programme that is deliverable in the home and community may assist more individuals with stroke to mobilise safely beyond their front door.

Resources for therapy-led rehabilitation are often time limited and vary across the UK [19]. Alternative approaches need to be sought for long-term therapy management post-stroke. Technology such as ARC shows promise in bridging the gap [2, 11]. The majority of previous ARC interventions have been delivered face-to-face leading to high costs. Incorporating self-management into an ARC training programme and encouraging self-monitoring, adherence and self-regulation could provide a more economical method of delivering this intervention.

In this pilot study, we aim to determine it is possible to deliver the study protocol over multiple sites in the home and community. This pilot study will be able to inform a future multi-centre observer blind parallel group randomised controlled trial (RCT) of the ARC treatment.

### Research aim

The primary aim of the ACTIVATE study is to determine the feasibility of a multi-centre (*n* = 4), observer blind, parallel group randomised controlled trial of ARC training to improve gait and physical activity after stroke.

### Study objectives

Primary objectives:
To identify monthly recruitment rates to determine whether it is possible to enrol at least one patient per month from each study centre.To report participant adherence to ARC intervention and control treatment arms (provider observation and exercise diaries).To assess the acceptability and completeness of proposed methods of data collection to ensure they are feasible for a definitive trial.

Secondary objectives:
4.To report participant retention to the study.5.To report the success of outcome assessor blinding to participant treatment allocation.6.To report adverse events in control and intervention treatments during the study.7.To report the views of study participants about undertaking the ARC intervention at home and in the community.8.To report the views of providers and clinical therapists about the study protocol.9.To gather data to allow reporting of summary statistics to allow estimation of the sample size requirements for the definitive trial.

### Progression criteria

Progression criteria have been set based upon recruitment, treatment adherence and data completeness to determine whether progression to a definitive trial is appropriate. These criteria and the traffic light system applied are based upon recommendations from Avery et al. [20].

Potential success criteria:
*Recruitment of participants*: green = an average of at least four patients per month recruited across the four sites; amber = an average of at least three patients per month recruited across the four sites; red = two or fewer patients recruited per month across the four sites.*Treatment adherence*: green = an average of at least 80% (840 out of 1080) supervised and self-monitored treatment sessions completed across the intervention and control treatment cohorts measured by provider observation and exercise diaries; amber = an average of at least 70% (756 out of 1080) supervised and self-monitored treatment sessions completed by participants; red = an average of 70% or less supervised and self-monitored treatment sessions completed by participants.*Data completeness:* green = completion (no missing data) of over 85% of key outcome measures (7 day accelerometer measurement; walking speed in the home; miniBEST and self-completion questionnaires: for full description see the ’Baseline assessment’ section) at 10-week outcome assessment for all those completing the treatment programmes; amber = completion of over 70% of key outcome measures at 10 weeks; red = completion of 70% or less of key outcome measures at 10 weeks.

Whilst these criteria will be used to evaluate the likely feasibility of a larger trial, they will primarily be employed to optimise the study design and identify/address issues in order to take remedial steps in a timely fashion. An example of this would be problems around recruitment.

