## Trial status

Patient recruitment and intervention began in November 2018. The ACTIVATE trial has recruited 16 participants out of our target of 60 at the time of submission of this manuscript (April 2019).

Protocol number and date: Version 2 dated 11.12.2018

Protocol Amendment number 1 Authors [name].

Revision chronology: 11.12.2017 original. 11.12.2018 Amendment number 1

Primary reason for amendment: changes in sections A27-1, A28 and A29 regarding increasing recruitment potential and additional recruitment materials.

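### The recruitment bands assign no colour to averages strictly between two and three per month, and adherence of exactly 70% is both amber and red

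*Protocol article*

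**What the plan says.** The Progression criteria section of the protocol article gives three traffic-light criteria.

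- **Recruitment.** Green is a mean of four or more a month, all sites together. The amber floor and the red ceiling then read "at least three patients per month recruited across the four sites; red = two or fewer patients recruited per month", again counted over all sites.
- **Adherence.** Green is worded as "green = an average of at least 80% (840 out of 1080) supervised and self-monitored treatment sessions completed". The middle band follows as "amber = an average of at least 70% (756 out of 1080) supervised and self-monitored treatment sessions completed by participants", while the lowest band is given as "red = an average of 70% or less supervised and self-monitored treatment sessions completed by participants".
- **Data completeness at 10 weeks.** Green is over 85%, amber over 70%, red 70% or less.

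The section gives the criteria two uses. They are to decide whether moving to a definitive trial is appropriate, and they are to be used primarily to improve the design and prompt timely remedial action, with recruitment as the example. The Sample size section plans 60 participants in 15 months at one per centre per month. The Data analysis section reports recruitment as a monthly rate, in total and per site. The Trial status section states: "The ACTIVATE trial has recruited 16 participants out of our target of 60", with recruitment starting in November 2018 and the manuscript submitted in April 2019.

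**The concern.** A traffic-light rule works only if each possible result receives exactly one colour. Two of the three criteria fail this.

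For recruitment, the measure is an average, so non-integer values are to be expected. Amber starts at three and red stops at two, and nothing covers the interval between. For adherence, amber and red both include 70%.

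Recruitment is the first primary objective, and the Data analysis section rules out statistical comparison of clinical outcomes between the treatments. These bands are therefore the main decision rule fixed in advance. If the recruitment result falls in the gap, someone must decide after seeing the data whether it counts as amber or red. The remedial use suffers too: at 2.5 per month the protocol does not say which signal has been given.

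**Working it through.** **Inputs.** Four centres, one patient per centre per month, 15 months, target 60 (Sample size). Eighteen sessions per participant in each arm (the two Dose and duration sections). Band limits (Progression criteria). Sixteen recruits, November 2018 to April 2019 (Trial status).

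**The plan's own figures.** Target: 4 × 1 × 15 = 60, reproduced. Planned sessions: 60 × 18 = 1080, reproduced. Amber adherence floor: 0.70 × 1080 = 756, reproduced. Green adherence floor: 0.80 × 1080 = 864, whereas the protocol prints 840, and 840/1080 = 77.8%. That count is not reproduced.

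**Recruitment bands as 15-month totals.**

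| Band | Monthly average | Total over 15 months |
|---|---|---|
| Green | at least 4 | 60 or more |
| Amber | at least 3, below 4 | 45 to 59 |
| No colour | above 2, below 3 | 31 to 44 |
| Red | 2 or fewer | 30 or fewer |

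The uncoloured range holds 44 − 31 + 1 = 14 integer totals, from 31/15 = 2.07 to 44/15 = 2.93 per month.

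**Adherence bands.** Checking every session total from 0 to 1080, with green taking precedence over amber, only 756 receives two colours. This holds whether green starts at 840 or 864. No total is uncoloured.

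**Data completeness bands.** Checking 0 to 100% in steps of 0.1 finds no gap and no overlap.

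**Where accrual stands.** Only months are given, so both counts are shown: 16/6 = 2.67 per month, inside the gap; 16/5 = 3.2 per month, just above it in amber.

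**Chance of finishing in the gap.** The documents give no accrual model. Assume the 15-month total is Poisson with mean 15 × rate; then P(31 to 44) = F(44) − F(30), where F is the Poisson distribution function.

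| True rate per month | Mean total | P(31 to 44) |
|---|---|---|
| 2.0 | 30 | 0.45 |
| 2.5 | 37.5 | 0.75 |
| 2.67 | 40 | 0.70 |
| 3.0 | 45 | 0.47 |
| 3.2 | 48 | 0.31 |
| 3.5 | 52.5 | 0.13 |
| 4.0 (planned) | 60 | 0.02 |

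These treat all 15 months as unobserved. Given the 16 already recruited, finishing in the gap needs 15 to 28 more. At 3.0 per month that has probability 0.40 with ten months left (mean 30) and 0.62 with nine (mean 27). The unconditional 0.47 lies between them, so these figures indicate size only.

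**The case against.** Several points on the other side stand, at least in part.

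- **Use of the criteria.** The protocol calls them potential success criteria and says they serve primarily to optimise the design. This lowers the stakes. It does not remove them, since the same section also uses the criteria to judge whether progression is appropriate, and a trigger for remedial action needs defined bands as well.
- **A shortfall would still be visible.** An average of 2.07 to 2.93 fails both green and amber as worded, and the monthly rate is reported in total and by site. Such a result could not be presented as meeting a stated threshold. What stays open is whether it is red or something milder.
- **Early accrual is a weak forecast.** The period may be five or six months, and the Trial status section records an amendment dated 11.12.2018 aimed at increasing recruitment potential. At the planned four per month the gap is very unlikely to be reached (0.02).
- **The adherence overlap is one value.** Only 756 of the possible totals is affected.

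A reader might infer that the whole traffic-light scheme is defective, or that the trial is heading for an undefined result. The documents support neither. Data completeness is properly partitioned, and the accrual figures fall on both sides of the amber floor depending on how the months are counted. A reader might also infer that the gap was plainly meant to be red. The protocol does not say so: closing it either way changes one of the two stated limits.

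**Conclusion.** The point holds for recruitment and, trivially, for adherence. Final recruitment totals of 31 to 44 have no colour, and no other section supplies one. The gap matters if the true rate is roughly two to three per month, where the assumed Poisson model gives about a 45% to 75% chance of finishing uncoloured. It matters little at the planned rate. Observed accrual of 2.67 to 3.2 per month is in or close to the gap. That rests on an imprecise number of months and should not be read as a prediction.

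The adherence overlap at 756 of 1080 is a plain contradiction of negligible probability. Since the criteria are used mainly to optimise the design and the remedy is wording only, this is a should-fix.

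**What to change.** Make the change before final totals are known.

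1. **Recruitment.** Close the gap at one cut-off. Either define red as below 3.0 per month, which keeps the stated amber floor and is the stricter option, or define amber as above 2.0 and below 4.0, which keeps the stated red ceiling. State which was chosen and why. Accrual to date is already known to be near three, so the reason should be recorded to show that the line was not placed to suit the result.
2. **Adherence.** Define red as below 70%, so that 756 of 1080 is amber only. Reconcile the green count with its percentage: 80% of 1080 is 864, and totals of 840 to 863 currently meet the printed count but not the printed percentage.
3. **Data completeness.** No change is needed to its boundaries.

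The cost is protocol wording only, with no effect on design, sample size or data collection. The downside is that averages between two and three per month become explicitly red or explicitly amber, so the sponsor gives up discretion over that range.

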### Sample size

We aim to recruit 60 participants in 15 months at a rate of one patient per trial centre per month. This sample size has been selected as it is the sample recommended for pilot studies [21]. We believe that this is a realistic recruitment rate informed by previous trials [22, 23].

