### Study intervention treatment: auditory rhythmical cueing and gait and balance exercises

#### Dose and duration

Participants will be asked to undertake three × 30-min ARC treatment sessions per week for 6 weeks (total 18 sessions). This dose and duration has been selected based on findings from previous laboratory-based studies investigating cueing after stroke [11] and on findings from our previous successful RCT in Parkinson’s disease [24].

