### Study control treatment: gait and balance exercises

#### Dose and duration

Control participants will undertake a matched dose of balance and gait exercise treatment sessions to the intervention treatment group, e.g. three × 30-min sessions per week for 6 weeks (total 18 sessions).

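### The green adherence threshold equates 80% with 840 of 1080 sessions, but 80% of 1080 is 864 and 840 is only 77.8%

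*Protocol article*

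**What the plan says.** The protocol article, under Progression criteria, sets a traffic-light rule for treatment adherence. The green band reads "green = an average of at least 80% (840 out of 1080) supervised and self-monitored treatment sessions", and the sessions counted are those "completed across the intervention and control treatment cohorts measured by provider observation and exercise diaries", so both arms are pooled. The next band reads "amber = an average of at least 70% (756 out of 1080) supervised and self-monitored treatment sessions completed by participants". The lowest reads "red = an average of 70% or less supervised and self-monitored treatment sessions completed by participants".

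The denominator of 1080 is not explained there, but its parts appear elsewhere in the article. Under Sample size: "We aim to recruit 60 participants in 15 months at a rate of one patient per trial centre per month". Under Dose and duration for the intervention: "ARC treatment sessions per week for 6 weeks (total 18 sessions". Under Dose and duration for the control, the dose is matched: "sessions per week for 6 weeks (total 18 sessions".

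Adherence in both arms is one of the three primary objectives. The section says the criteria bear on whether a definitive trial should follow, and that their main use is to improve the design and prompt timely remedies.

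**The concern.** The green band gives one threshold in two forms, a percentage and a count, and the two do not agree. A threshold fixed in advance is useful only if it gives one answer for each possible result. Here a range of results just below 80% is green by the count and amber by the percentage, so whoever reports the trial could choose the colour after seeing the data. The error favours the trial: read by the count, the green bar is lower than the stated 80%.

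A second weakness is that both counts are tied to exactly 60 participants. If another number is randomised, the counts no longer correspond to the percentages, and the text does not say which form takes precedence.

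**Working it through.** **Inputs**
- Planned participants: 60 (Sample size).
- Sessions per participant: 3 per week × 6 weeks = 18, in each arm (Dose and duration, intervention and control).
- Green: at least 80%, given as 840 of 1080. Amber: at least 70%, given as 756 of 1080 (Progression criteria).

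**Reproducing the article's own figures**
- Denominator: 60 × 18 = 1080. Agrees.
- Amber: 0.70 × 1080 = 756. Agrees exactly.
- Green: 0.80 × 1080 = 864. Does not agree with 840.
- The stated green count as a percentage: 840 / 1080 = 77.8%.

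**Could 840 come from another denominator?** For 840 to be exactly 80%, the denominator would have to be 840 / 0.80 = 1050 sessions, and 1050 / 18 = 58.33 participants. No whole number of participants gives this: 58 gives 0.80 × 1044 = 835.2, and 59 gives 0.80 × 1062 = 849.6. Rounding does not explain it either, since 864 is already a whole number.

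**Size of the discrepancy**
- 864 − 840 = 24 sessions; 24 / 1080 = 2.2 percentage points.
- Per participant: 840 / 60 = 14.0 sessions against 864 / 60 = 14.4.
- Totals with two colours: 840 to 863, which is 24 values, from 77.8% to 863 / 1080 = 79.9%.

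**What happens to the counts if fewer than 60 are randomised** (the numbers randomised below are illustrative assumptions)

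| Randomised | Maximum sessions | 840 as % of maximum | 756 as % of maximum |
|---|---|---|---|
| 60 | 1080 | 77.8% | 70.0% |
| 58 | 1044 | 80.5% | 72.4% |
| 48 | 864 | 97.2% | 87.5% |
| 46 | 828 | not reachable | 91.3% |
| 40 | 720 | not reachable | not reachable |

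The counts become steadily stricter than the percentages as the number falls. The count of 840 cannot be reached with 46 or fewer participants (46 × 18 = 828), nor 756 with 41 or fewer (41 × 18 = 738).

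**The case against.** Nobody can defend the arithmetic, so the case on the other side is about weight.

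- **Use of the criteria.** The article presents them as potential criteria, used mainly to improve the design. No hypothesis test, sample size or participant's care depends on 840. This stands as a limit on the consequences. It does not remove the problem, because the same section gives the criteria a part in deciding on a definitive trial.
- **Reach of the conflict.** Only 24 totals are affected, and they move between green and amber. None is near the red limit, so no red result is created or hidden. This is correct.
- **Which figure governs.** The percentage comes first and the count is in brackets, so a reader would naturally take 80% as the rule. On that reading the bar does not move when the count is corrected. This is reasonable, but the article does not say so, and the count is the more concrete figure to apply.
- **Numbers other than 60.** The counts can be read as an illustration at the target, with the percentage still usable otherwise. That is fair, and it supports stating that the percentage governs. The criterion as a whole does not collapse below 60; only the counts do.
- **The denominator for people who stop treatment.** How their sessions are counted could be left to a fuller document. However, 18 sessions for every participant is the construction that already produces 1080, so writing it down adds nothing new.

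A neighbouring defect also survives correction of the count: exactly 70% satisfies both the amber and the red wording.

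**Conclusion.** The concern holds. The green count is wrong on the article's own numbers: 80% of 1080 is 864, and the stated 840 is 77.8%. The discrepancy is 24 sessions (2.2 percentage points), and totals of 840 to 863 receive two colours. This rests on 1080 being 60 × 18, which the article's sample size and session numbers support and which the exact amber count confirms.

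That 840 is a slip for 864 is an inference. It is the natural one, because the percentage is the leading figure and the amber count matches its own percentage. If 840 was what the authors intended, the percentage would have to read about 77.8%. Either way the text cannot stand as printed. The practical effect is confined to results just under 80%, but it falls on a pre-stated threshold for a primary objective.

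**What to change.** - Replace 840 with 864 in the green adherence band.
- Add a clause stating that the percentage governs and that its denominator is 18 times the number of participants randomised, with the counts shown only as an illustration for 60.
- In the same edit, make amber and red mutually exclusive at exactly 70% (756 of 1080), for example by defining red as below 70%.

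The cost is one figure and one clause, plus the small wording change at 70%. Nothing changes in conduct, data collection or participant burden. For anyone who had been working to the count, the green bar rises by 24 sessions; for anyone working to the percentage, it stays where it was. Because the article reports that recruitment had already begun, the correction should be dated and made without reference to accumulated adherence data.

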#### Mode of delivery

The ARC intervention treatment will be delivered by two providers (a research physiotherapist and a research associate). The treatment providers will supervise six of the ARC treatment sessions over the 6 weeks. The other 12 ARC treatment sessions will be undertaken independently by participants with telephone support from the treatment providers as necessary (maximum 6 telephone calls). All exercises will initially be supervised in order to determine whether participants are safe to undertake the exercises independently. All community walking sessions with the ARC device will be supervised to ensure safety.

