### Data analysis

Objectives 1–3: Recruitment will be described as rate/month (total and per site). Adherence will be described using data from the exercise diaries (number of planned sessions completed). Acceptability and completeness of methods of data collection will be described using percentages from both treatments.

Objective 4: Retention will be described as percentage from both treatments.

Objective 5: The success of outcome measurement blinding will be described (%).

Objective 6: Adverse events pertaining to the study for each treatment will be described (number of events).

Objective 7: The views of study participants about undertaking the ARC treatment at home and in the community will be described. Summary statistics will be used for answers to closed questions and open questions will be thematically analysed.

Objective 8: The views of providers and clinical therapists about delivery of the study treatments will be described. Summary statistics will be used for answers to closed questions and open questions will be thematically analysed.

Objective 9: As this is a pilot study, statistical comparisons of clinical outcomes (e.g. dynamic gait index, see above) and accelerometer data between treatments will not be undertaken and data will be presented as summary descriptive statistics. To determine which outcome measures to take forwards to a main trial, we plan to review data completeness, patient/staff feedback about acceptability and any new emerging literature about most appropriate measures, to inform decisions. This review will also determine the most appropriate primary outcome measure. Data collected for this selected primary outcome measure (e.g. standard deviation) will subsequently be used as appropriate by statisticians to inform a power calculation for a definitive trial.

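### The adherence light pools supervised and self-managed sessions, so good supervised attendance can show amber while self-managed practice is at the plan's own red level

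*Protocol article*

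**What the plan says.** Under Progression criteria, the protocol article sets one traffic light for treatment adherence. It rests on the average share of "supervised and self-monitored treatment sessions completed across the intervention and control treatment cohorts measured by provider observation and exercise diaries". Green is at least 80% (printed as 840 of 1080), amber at least 70% (756 of 1080) and red 70% or less.

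The sessions are of two kinds. For the ARC arm, Mode of delivery states: "The treatment providers will supervise six of the ARC treatment sessions over the 6 weeks". It continues: "The other 12 ARC treatment sessions will be undertaken independently by participants". The control arm has the same 18-session dose. Its Mode of delivery section describes weekly contact, face to face or by telephone, and leaves the other 12 sessions to be done independently.

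The Background gives self-management as part of the rationale: "Incorporating self-management into an ARC training programme and encouraging self-monitoring, adherence and self-regulation could provide a more economical method of delivering this intervention". No threshold is set for the self-managed sessions alone. The Data analysis section, for objectives 1 to 3, states: "Adherence will be described using data from the exercise diaries (number of planned sessions completed". It mentions no division by session type.

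**The concern.** The two kinds of session answer different feasibility questions. A supervised session takes place with a provider present and is counted by provider observation. A self-managed session depends on the participant practising alone and is counted from a diary. Twelve of the 18 sessions are of the second kind, and that part bears on whether the programme could be delivered more cheaply.

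A pooled percentage lets a high supervised rate offset a low self-managed one. The team could then read amber, adherence acceptable with some adjustment, when self-managed practice taken alone would be red. The total also cannot show which component needs a remedy, although the same section says the criteria are mainly for optimising the design and finding problems. The effect arises within each arm, so it is separate from the pooling of the two arms.

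**Working it through.** **Inputs.** 60 participants (Sample size). 18 sessions per participant in each arm (both Dose and duration sections). In the ARC arm, 6 supervised and 12 self-managed (Mode of delivery). In the control arm, 12 independent sessions. The main calculation assumes that the control arm's six weekly contacts count as supervised sessions; this is varied below.

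**The plan's own figures.**
- Total: 60 × 18 = 1080, as printed.
- Amber: 0.70 × 1080 = 756, as printed.
- Green: 0.80 × 1080 = 864, against a printed 840. 840/1080 = 77.8%. This mismatch is a separate error, so both values are carried.

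**Split.** Supervised: 60 × 6 = 360. Self-managed: 60 × 12 = 720.

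**Formula.** With threshold count G and supervised completion s, the self-managed adherence needed to reach the threshold is (G − 360s)/720.

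| Supervised completion s | Amber, G = 756 | Green, G = 864 (true 80%) | Green, G = 840 (printed) |
|---|---|---|---|
| 100% | 396/720 = 55.0% | 504/720 = 70.0% | 480/720 = 66.7% |
| 95% | 414/720 = 57.5% | 522/720 = 72.5% | 498/720 = 69.2% |
| 90% | 432/720 = 60.0% | 540/720 = 75.0% | 516/720 = 71.7% |

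**Where masking starts.** Set self-managed adherence to 70% (504 sessions) and solve for s.
- Amber: (756 − 504)/360 = 70.0%. Whenever supervised completion exceeds 70%, the pooled light can be amber with self-managed adherence below 70%.
- Green at 864: (864 − 504)/360 = 100%. Green meets 70% self-managed adherence only if every supervised session is done.
- Green at 840: (840 − 504)/360 = 93.3%.

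**ARC arm alone**, where the split is explicit: 30 participants give 540 sessions, of which 180 are supervised. With all of those done, amber needs (378 − 180)/360 = 55.0% and a true 80% needs (432 − 180)/360 = 70.0%. The control-arm assumption does not affect these.

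**Control contacts all by telephone and counted as self-managed.** Supervised 180, self-managed 900, all supervised sessions done.
- Amber: (756 − 180)/900 = 64.0%, still in the red band.
- Green: (864 − 180)/900 = 76.0%, or (840 − 180)/900 = 73.3% on the printed count. Neither is red.

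**The case against.** The treatment under test is the whole 18-session package, so total dose received is a legitimate adherence measure, and the 80% and 70% bands were written for that total. The plan nowhere requires 80% of the self-managed part. This stands: a self-managed band would be a new requirement.

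A reader might infer that the light can readily be green while self-managed adherence is red. The documents do not support that. At a true 80% it needs every supervised session completed and self-managed adherence of exactly 70.0%, a value that the plan's wording places in both amber and red. At 95% supervised completion, green already needs 72.5%, which is amber. The apparent range from 66.7% to 70% comes only from the printed 840 and goes once that count is corrected.

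Simulation does not rescue the stronger reading. Take, as assumptions, true self-managed adherence of 70%, a between-participant SD of 0.2 or 0.3, and full supervised completion. Pooled green at 864 then occurs in about 51% of trials, but only because the cut-off equals the simulated mean. Trials that are green with observed self-managed adherence of 70% or less make up 1% to 2%, and none at 95% supervised completion.

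Three further points soften the matter. The control split is not firm, because weekly contact may be by telephone. The criteria are described as potential and mainly for optimising the design, not as a mechanical stop rule. A breakdown by session type is reporting detail that a condensed article may leave to a fuller document, and the planned interviews cover engagement with independent sessions. None of these changes the amber result, because the pooled rule itself is fixed in the article.

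**Conclusion.** The point holds for amber and, in a weaker form, for green. Amber can be reached with self-managed adherence of 55.0% to 60.0% when supervised completion is between 100% and 90%, and with 64.0% on the all-telephone reading of the control arm with all supervised sessions done. Each figure is red on the plan's own scale. For a true 80% green, pooling lowers the self-managed rate needed to between 70.0% and 75.0%, and this coincides with red only at the boundary.

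These results are exact arithmetic on the planned 60 participants and 18 sessions each. They assume supervised completion of 90% or more, which the documents do not forecast, and, except for the ARC-only and telephone calculations, a 6/12 split in both arms. This is a worthwhile, low-cost improvement to what the light can tell the team. It does not show that the criterion is invalid as a measure of total dose.

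**What to change.** In Progression criteria, keep the pooled total and also apply the adherence bands to self-managed sessions in their own right (diaries, 12 per participant). Green should require both to reach the green band. Show the self-managed colour beside the pooled one, so that a red self-managed rate under an amber total is visible.

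In Data analysis, report supervised and self-managed completion separately by arm. State whether a control-arm weekly telephone contact counts as a supervised session, since this decides the self-managed denominator in that arm. Say openly that the self-managed band is an addition to bands set for total dose.

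The cost is wording. Provider records and exercise diaries are already collected, and no treatment, visit or dose changes. The downside is that green becomes harder to reach. The printed 840 should be reconciled with 80% at the same time, as a separate correction.
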